### Control variables

It has been widely demonstrated that the work environment and its characteristics can influence employee well-being. For instance, studies have shown that some psychological risk factors in the workplace positively or negatively predict burnout and vigor [67]. In the same vein, research grounded in SDT has shown that a work environment supporting the employees’ three basic psychological needs helps develop autonomous motivation and well-being at work while an environment that frustrates these needs is related to controlled motivation and employee ill-being (for a review, see [68]). As a result, we will control for the job characteristics and the employees’ work need satisfaction in order to test the true effect of the intervention on the changes in job well-being.

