### Measures

Table 1 provides an overview of the measurement points of the primary and secondary outcomes, mediators, moderators and control variables, and manipulation check variables. At the end of the second session of each week, participants will complete a questionnaire measuring their weekly burnout, vigor, needs satisfaction at work and workload, as well as recovery mechanisms experienced, affects and effort perception during sessions (only for the 3 intervention groups). Five minutes are requested to complete the questionnaire. In week six of the program, participants will complete an online survey measuring job characteristics, and intervention groups will wear a 3-axis accelerometer to assess their energy expenditure during PA or theatre sessions. In week eight of the intervention, all instructors will be recorded audio-visually and participants will complete an online survey assessing their instructor’s motivational style during the sessions. At the beginning of the final session of the intervention participants will replicate the cardiorespiratory fitness test, and at the end of the intervention, participants will complete an online survey measuring the same variables as those assessed at baseline. Finally, three and six months after the end of the intervention, participants will be invited to complete the follow-up online questionnaire. In order to measure the *compliance* to the program, instructors from the three intervention groups will be asked to indicate the participants’ presence or absence at each session in a register.

**Table 1 Tab1:** Overview of the measurement points for the primary and secondary outcomes, during intervention and weekly measures, and follow-up measurements

	Variables	Pre-intervention (T0)	During intervention (T6 or T8)	Weekly (T1-T10)	Post-intervention (T11)	Follow-up at 3 and 6 months (T12–13)
Primary outcomes	− Burnout	✓		✓	✓	✓^a^
	− Vigor	✓		✓	✓	✓^a^
Secondary outcomes	− Job satisfaction	✓			✓	✓^a^
	− Work motivation	✓			✓	✓^a^
	− Work performance	✓			✓	✓^a^
	− Work ability	✓			✓	✓^a^
Psychological and physiological mediators	− Off-job recovery activities	✓			✓	
	− Psychological detachment	✓		✓^a^	✓	
	− Relaxation	✓		✓^a^	✓	
	− Control	✓		✓^a^	✓	
	− Mastery	✓		✓^a^	✓	
	− Relatedness	✓		✓^a^	✓	
	− Positive Affects			✓^a^		
	− Cardiorespiratory Fitness	✓			✓	
Moderator variable	− Compliance to activity sessions			✓^a^		
Control variables	− Job characteristics	✓	✓(T6)	✓^b^	✓	

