	− Needs satisfaction at work	✓	✓(T6)	✓	✓	
	− Workload at work			✓		
Manipulation check	− Instructors observed motivating style		✓(T8)			
	− *participants’ perception of the instructor’s motivating style*		✓(T8)			
	− Objective effort during sessions		✓(T6)			
	− Perceived effort during sessions			✓^a^		

^a^Variables only collected in intervention groups; ^b^Variables only collected in the waiting-list group

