#### Control variables

##### Job characteristics

Job characteristics will be assessed with 12 items from the French short version of the Copenhagen Psychosocial Questionnaire [86]. Designed to assess psychosocial risk factors at work, the original version has 46 items grouped in 24 scales referring to six dimensions: quantitative demands, autonomy, organization and leadership, horizontal relationships, work attitudes, and work-related well-being. In this study, we will remove scales that are inappropriate regarding the employment of future participants, and we will assess only one single-item per scale in order to reduce the length of this questionnaire. In addition, we will not measure the work-related well-being dimension which includes scales close to our primary and secondary outcomes. Thus, the “quantitative demands” dimension has three single-items assessing *workload* (“Do you have enough time for your work tasks?”), *work pace* (“Is it necessary to keep working at a high pace?”), and *cognitive demands* (“Does your work require that you remember a lot of things?”). The “organization and leadership” dimension has four single-items assessing *predictability* (“Do you receive all the information you need in order to do your work well?”), *recognition* (“Is your job recognized and appreciated by the management?”), *role clarity* (“Do you know exactly what is expected of you at work?”) and *social support from supervisor* (“Is your supervisor ready to listen to you about work problems”). The “horizontal relationships” dimension has one single-item assessing *social support from colleagues* (“Do your colleagues listen to your problems at work?”). The “autonomy” dimension has two single-items assessing *influence* (“Can you influence the amount of work assigned to you?”) and *possibilities for development* (“Do you have the possibility of learning new things through your work?”). The “work-individual interface” dimension has two single-items assessing *meaning of work* (“Do you feel that the work you do is important?”) and *job satisfaction* (“How pleased are you with your job as a whole, everything taken into consideration?”)*.* Participants will answer these items with a seven-point scale (1 = strongly disagree, 7 = strongly agree). The validity and reliability of this tool were satisfactory and have been reported by Dupret et al. [86].

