### Statistical analysis

#### Analyses of Primary and secondary outcomes

Between-arm differences in changes on the primary and secondary outcomes will be analyzed using generalized linear mixed models (GLMM) according to intention-to-treat and per-protocol principles. Intention-to-treat analyses [91] refer to the effect of treatment “as assigned”, meaning that all participants who are randomized to a condition will be included in the analyses, regardless of dropout or missing values. By contrast, per-protocol analyses refer to the effect of treatment “as received”, excluding only participants who have less than 50% compliance to the 20 sessions in the intervention. GLMM has several advantages over repeated measures ANOVA as it considers the hierarchical nature of the data and can accommodate missing data [92]. To distinguish between short- and long-term intervention effects, two separate series of GLMM analyses were performed for each outcome variable. Two time points (pre and post) were used to determine short-term intervention effects and four time points (pre, post, three- and four-month follow-ups) were used to examine long-term intervention effects. Regarding the short-term intervention effects, differences in changes on the outcome variables as a function of the group allocation will be assessed with models including group, time, and group x time interaction as fixed effects. For the group allocation, contrasts analyses [93] will also be carried out to test our hypotheses (H1 – H4) specifically. For that, three contrasts will be computed. The first one will compare the WLC condition with the Theatre condition, PA-TS and PA-NSS conditions (respectively coded as − 0.75, + 0.25, + 0.25, + 0.25) to test whether doing a leisure activity (PA or Theatre conditions) at the workplace leads to a reduction in burnout and an improvement in vigor (H1a, H1b). The second contrast will compare the Theatre condition with the PA-TS and PA-NSS conditions (respectively coded as − 0.667, + 0.333, + 0.333, while WLC will be coded 0) to test whether PA is more effective than theatre condition (H2) in reducing burnout and improving vigor. Finally, the third contrast will compare the PA-TS condition with the PA-NSS condition (respectively coded as − 0.50, + 0.50, while WLC and Theatre conditions will be coded 0) to test whether the positive effect of PA is more pronounced when the instructor uses a need-supportive style (H3). The same analyses will be performed to examine if the effects of the intervention are still effective three months (T12) and six months (T13) after the end of the intervention period. Since there are more than two-time measurements per participant, we will allow random intercepts for participants and random linear slopes for the repeated measurements at the level of participants. These random effects will allow us to estimate each participant’s outcome variables and the rate of change of these outcomes over time. In all analyses we will control for a number of variables that could influence participants’ outcomes. These include job characteristics, and needs satisfaction-frustration at work. Finally, an estimate of the effect size for each outcome will be reported using the conditional pseudo R^2^, which will be computed using the MuMin package of the R software [94].

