#### Analyses of Weekly trajectories

To investigate the trajectories of weekly variables over the intervention period (H6a, H6b, H6c), we will use growth models in a multilevel modelling framework. Two models will be tested for burnout and vigor respectively. They will contain a random intercept and a random linear slope for the occasion of measurement at the subject level. This random slope for occasion measurements will allow each participants’ growth trajectory over time to be estimated. A linear and quadratic effect of occasion measurements will be added as fixed effects to examine the linear and accelerated evolution of the outcomes over time. The three orthogonal contrasts will be added as fixed factors to the model, as well as their interaction terms with “time” and “time2”. Thus, we will examine if there is an effect of the intervention (H6a), the type of activity or need-supportive style (H6b) on the level of and rate of change in burnout and vigor over time. In all analyses we will control for variables that could influence participants’ outcomes, such as weekly needs satisfaction-frustration at work and weekly workload.

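### The weekly trajectory models for H6a and H6b adjust for self-reports collected after randomisation, and the main outcome models leave the timing of their covariates open

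*Protocol article*

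**What the plan says.** **Weekly models.** *Analyses of Weekly trajectories* fits growth models for burnout and vigor, with the three group contrasts and their interactions with time and time squared. All of these models control for variables "such as weekly needs satisfaction-frustration at work and weekly workload". Under *Work-related variables*, weekly burnout, vigor, needs satisfaction and workload form one ten-item questionnaire. In the activity arms it is completed after the second session of the week; the waiting-list arm answers online.

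**Main models.** *Analyses of Primary and secondary outcomes* states: "In all analyses we will control for a number of variables that could influence participants’ outcomes". It then adds: "These include job characteristics, and needs satisfaction-frustration at work". No measurement occasion is given. Table 1 ticks both covariates at T0, T6 and T11, and neither at the three- and six-month follow-ups. The text of *Measures* agrees for job characteristics: "In week six of the program, participants will complete an online survey measuring job characteristics". For the end of the programme it says that "participants will complete an online survey measuring the same variables as those assessed at baseline".

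**Content of the covariate set.** *Job characteristics* leaves out the questionnaire's well-being dimension because it contains scales close to the trial's outcomes. It keeps, under another dimension, the item "How pleased are you with your job as a whole, everything taken into consideration". Job satisfaction is a secondary outcome that H4a expects to improve.

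**Purpose.** The *Control variables* section of the Background says the adjustment is made "in order to test the true effect of the intervention on the changes in job well-being".

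**The concern.** Randomisation protects a between-arm comparison as long as the model conditions only on what was fixed before allocation. A covariate measured during treatment may itself respond to treatment. Adjusting for it then takes out the part of the effect that runs through it. If the covariate and the outcome also share unmeasured causes, such as mood when the questionnaire is filled in, adjustment adds a bias of its own.

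The weekly covariates are open to this. Needs satisfaction at work covers feeling competent, autonomous and supported by colleagues. The participants are employees of one university who meet in groups on campus twice a week. A change in how supported or competent they feel at work is plausible, though the protocol does not predict it.

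At stake is what H6a and H6b can claim. They are worded as differences between conditions in weekly burnout and vigor, and the adjusted terms would answer a different question. If the main models were run with T6 or T11 covariates, H1 to H4 would be affected too, and for H4a the adjustment would be for nearly the same construct as the outcome.

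**Working it through.** **1. Which models use values collected after randomisation?**

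- *Weekly models (H6a, H6b):* stated. The covariates are weekly needs satisfaction and weekly workload, from T1 to T10.
- *Pre/post models (H1 to H4):* not stated. T0, T6 and T11 values all exist.
- *Long-term models:* not stated. No control variable is ticked at T12 or T13, so concurrent adjustment is impossible at those visits.

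**2. What does the adjustment remove?** The plan gives no figure for this, so the inputs other than d are assumptions.

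- d = 0.35, the effect used in *Sample size*. It serves only as a yardstick, since it was not set for the weekly models.
- a = shift in the covariate caused by the programme, in SD: 0 to 0.3 (assumed).
- b = size of the covariate–outcome slope, in SD per SD: 0.3 to 0.5 (assumed), signed so that an improved covariate goes with an improved outcome.

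Effect left after concurrent adjustment = d − a × b. Share removed = a × b / d.

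| a | b | a × b | effect left | share removed |
|---|---|---|---|---|
| 0 | any | 0 | 0.35 | 0% |
| 0.1 | 0.3 | 0.03 | 0.32 | 9% |
| 0.1 | 0.5 | 0.05 | 0.30 | 14% |
| 0.2 | 0.3 | 0.06 | 0.29 | 17% |
| 0.2 | 0.5 | 0.10 | 0.25 | 29% |
| 0.3 | 0.3 | 0.09 | 0.26 | 26% |
| 0.3 | 0.5 | 0.15 | 0.20 | 43% |

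The same algebra applies to the growth terms. If the programme moves the covariate by a0 + a1 × time, the contrast loses b × a0 and the contrast-by-time term loses b × a1.

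**3. Check by simulation.** This used two arms of 40,000, a pre/post change score and a true effect of 0.35. It tests the mechanism and does not reproduce the ten-week model.

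| a, b | unadjusted | T0 covariate | concurrent covariate |
|---|---|---|---|
| 0, 0.3 | 0.346 | 0.345 | 0.345 |
| 0.1, 0.3 | 0.353 | 0.353 | 0.324 |
| 0.2, 0.3 | 0.350 | 0.350 | 0.288 |
| 0.2, 0.5 | 0.345 | 0.344 | 0.246 |
| 0.3, 0.5 | 0.342 | 0.343 | 0.192 |

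T0 adjustment leaves the effect intact in every scenario. Concurrent adjustment removes a × b; in the last row, for example, 0.342 − 0.192 = 0.150.

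**4. Direction.** The table assumes that the programme improves the covariate, which shrinks the estimated benefit. If it made workload feel heavier, a would be negative and adjustment would enlarge the estimated benefit. Unmeasured shared causes can also push the estimate either way.

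**The case against.** The strongest reply is that the control variables describe the work environment. The protocol treats them that way, and none of its hypotheses predicts that the programme changes needs satisfaction at work or workload. If a = 0, nothing is removed and the adjustment only gains precision. This stands as a limit on the size of the bias. It does not justify the choice, because a = 0 is an assumption that T0 covariates make unnecessary.

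Several stronger readings are tempting, and the documents do not support them:

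- *Every efficacy model adjusts for values collected after randomisation.* Only the weekly section says so. The main section gives no occasion, T0 values exist, and an article may leave covariate timing to a fuller document. In the other direction, the mediation section names baseline explicitly where it means baseline, and both covariates are re-measured under the heading of control variables. Time-varying use is therefore a fair reading, but no more.
- *The job-satisfaction item breaks a stated rule.* The protocol drops one named dimension because it contains scales close to the outcomes, and the retained item belongs to another. Keeping it sits badly with that reasoning, but it does harm only if post-baseline values enter the H4a model. As a T0 covariate it is harmless.
- *Weekly job characteristics cannot serve as a common covariate.* The footnote "Variables only collected in the waiting-list group" is correctly read, but no stated model uses weekly job characteristics.
- *Missing covariates undermine intention-to-treat.* Weekly covariates share a questionnaire with the weekly outcomes, and T11 covariates are collected along with the T11 outcomes. Someone missing one would usually miss the other, so little extra is lost.

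**Conclusion.** The point holds for the weekly trajectory models. As written, the H6a and H6b contrasts condition on self-reports taken during treatment alongside the outcome, and they estimate the effect of allocation only if the programme leaves those self-reports unchanged. For the primary and secondary outcome models the same error is possible but not established. The job-satisfaction item is a poor choice of covariate, and becomes harmful only if used after baseline.

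The size is uncertain. Over the assumed ranges (a = 0.1 to 0.3, b = 0.3 to 0.5), 9% to 43% of an effect of 0.35 would be removed. At a = 0 none would be. No figure in the protocol narrows this range, and the direction is not fixed either. It should be corrected. It does not show that the planned primary analysis is biased.

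**What to change.** In *Analyses of Weekly trajectories*, remove weekly needs satisfaction and weekly workload from the models that test H6a and H6b. Use T0 needs satisfaction and T0 job characteristics instead; the latter already include a workload item. Models with the weekly covariates may still be reported, labelled exploratory and not presented as the effect of the intervention.

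In *Analyses of Primary and secondary outcomes*, state that job characteristics and needs satisfaction enter at their T0 values only, and drop the job-satisfaction item from the covariate set.

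The cost is a change of wording. The T0 values are already collected, and the sample size section uses no covariates, so the planned number is unaffected. The one downside is somewhat more residual variance in the weekly models, because week-to-week variation in needs and workload would no longer be absorbed.

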### Sample size

Sample size calculations were based on an a priori power analysis based on a previous study carried out on similar primary outcomes in the workplace [37, 66]. This study has reported a positive effect of the PA intervention on the emotional exhaustion component of burnout, with a small effect size (η^2^ = 0.03; f = 0.176). According to this result, we conducted an analysis with G*Power software [70] examining the evolution of burnout and vigor depending on the conditions as inter-individual factors, with an moderate effect size of d = 0.35, a statistical power of 80%, a threshold of significance at *p* < 0.025 considering our two primary outcomes, a correlation of .5 across repeated measures, and a potential dropout rate of 25% for a 10-week program with 4 groups. The results of this analysis recommend recruiting a minimum of 140 participants, 35 per group.

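### The planned effect size, a conditional pseudo R-squared, mostly measures how stable participants are and would be about 0.5 with no intervention effect at the plan's own correlation of 0.5

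*Protocol article*

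**What the plan says.** Under Analyses of Primary and secondary outcomes, the protocol article states that "an estimate of the effect size for each outcome will be reported using the conditional pseudo" R-squared, using a named R package. It is the only effect-size measure named in that section.

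The same section describes what the statistic would summarise:

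- The short-term analysis uses pre and post scores in "models including group, time, and group x time interaction as fixed effects".
- For analyses with more than two measurements, "we will allow random intercepts for participants and random linear slopes for the repeated measurements at the level of participants".
- All analyses adjust for further variables: "These include job characteristics, and needs satisfaction-frustration at work".
- Three contrasts carry the hypotheses: any activity against waiting list, physical activity against theatre, and need-supportive against traditional style.

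The Sample size section expresses the expected effect on a different footing. It cites eta-squared 0.03 (f = 0.176) from earlier work, plans on "an moderate effect size of d = 0.35", and assumes "a correlation of .5 across repeated measures".

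**The concern.** A conditional R-squared is the share of total variance accounted for by the fixed effects and the random effects together. Once participants have random intercepts, stable differences between people enter the numerator. Two people who differ by the same amount before and after the programme raise the statistic, although the programme did nothing to either of them.

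It is also a property of the whole model. Time, covariates and all four arms contribute, so one value per outcome says nothing about the size or direction of any of the three contrasts.

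This affects interpretation. A value near 0.5 labelled as an effect size would look very large beside the planning value of eta-squared 0.03, whether or not the intervention worked. Readers could not recover from it the quantity on which the trial was planned.

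**Working it through.** **Inputs.** From the Sample size section: within-person correlation 0.5, four groups, 35 per arm, d = 0.35, alpha 0.025, power 80%, dropout 25%. From the analysis section: group, time and their interaction as fixed effects, participant random effects, and two time points in the short-term model. The random part of the two-time-point model is not spelled out, so a random intercept is assumed.

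**The plan's own figure.** No R-squared value is stated; the computed figure is the sample size. Take f = d/2 = 0.175 and a repeated-measures interaction test with noncentrality f² × N × m/(1 − ρ), where m = 2 time points and ρ = 0.5. For N = 112 this is 0.030625 × 112 × 2/0.5 = 13.72, which gives power 0.81. The smallest N reaching 80% is 111, or 112 for equal groups, and 112 × 1.25 = 140. The planned effect is therefore an interaction of f = 0.175 at correlation 0.5.

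**Definitions.** Let F be the variance of the fixed-effect predictions, B the participant variance and E the residual variance.

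- Conditional R-squared = (F + B)/(F + B + E)
- Marginal R-squared = F/(F + B + E)

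**No effect.** Scale the total variance to 1. A correlation of 0.5 then means B = 0.5 and E = 0.5. With F = 0, conditional R-squared = 0.5/(0.5 + 0.5) = 0.50 and marginal R-squared = 0. In general, the no-effect conditional value equals the within-person correlation.

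**With an effect.** Suppose all three active arms shift by δ SD at post and the waiting list does not move. Three of the eight arm-by-time cells are displaced, so F = δ² × (3/8) × (5/8) = δ² × 15/64. The interaction effect is f = δ × √(3/64) = 0.2165 δ.

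| δ (SD) | f | F | Conditional | Marginal |
|---|---|---|---|---|
| 0 | 0 | 0 | 0.50 | 0.00 |
| 0.35 | 0.076 | 0.029 | 0.529/1.029 = 0.51 | 0.029/1.029 = 0.03 |
| 0.70 | 0.152 | 0.115 | 0.615/1.115 = 0.55 | 0.115/1.115 = 0.10 |
| 0.80 | 0.173 | 0.150 | 0.650/1.150 = 0.57 | 0.150/1.150 = 0.13 |

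**Simulation of the fitted model.** Settings: 35 per arm, two time points, correlation 0.5, random intercept, 4,000 runs per row. Estimated fixed effects add a little noise variance, so the means sit slightly above the formula.

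| δ (SD) | Mean conditional (95% range) | Mean marginal |
|---|---|---|
| 0 | 0.51 (0.38–0.63) | 0.02 |
| 0.35 | 0.52 (0.40–0.64) | 0.05 |
| 0.70 | 0.56 (0.44–0.66) | 0.12 |
| 0.80, about the planned f | 0.57 (0.46–0.67) | 0.15 |

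**Sensitivity, no effect.** With two time points, the mean conditional value is 0.32, 0.51, 0.70 and 0.80 for correlations of 0.3, 0.5, 0.7 and 0.8. With 26 per arm (about 25% dropout) and correlation 0.5 it is again 0.51. A small run of the four-time-point model with random slopes (12 runs per setting, 26 per arm) gave 0.52 without true slope variance and 0.56 with a slope SD of 0.2, both at correlation 0.5. At correlation 0.7 with a slope SD of 0.2 it gave 0.73. None of these runs includes the covariates.

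**The case against.** Five points can be made for the plan.

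1. **The value of 0.5 is conditional.** It rests on a planning correlation and on a random intercept that the article does not spell out for the pre–post model. This stands as a qualification. At other correlations the no-effect value runs from about 0.3 to 0.8, which is still large for a null trial. The longer-term models state their random effects explicitly, and there it is no lower.
2. **A 0.35 SD shift in three arms is not the planned effect.** It corresponds to f = 0.076, well under 0.175. That is correct, so the planned effect is represented above by the 0.80 SD row. Even there the conditional value rises only from 0.51 to 0.57, with overlapping ranges.
3. **The contrasts will be computed anyway, and a condensed article need not list every estimate.** This is fair, and nothing says those estimates will be withheld. The objection here is to a stated choice: the article names one measure as the effect size, and that measure does not size the effect.
4. **Nothing inferential changes.** True. The tests, the alpha and the sample size do not depend on it.
5. **Standardising by the baseline SD has its own weakness.** Eligibility is set on the primary outcomes (burnout at least 1.79, vigor at most 5.00), which may narrow the baseline SD and enlarge a standardised difference. This is a minor caveat, and a reason to put the scale-point estimate first.

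**Conclusion.** The concern holds. The measure named as the effect size mainly reflects within-person stability. At the plan's correlation of 0.5 it averages about 0.51 with no intervention effect and about 0.57 at the effect behind the 140 participants, so a single reported value could not separate the two situations. Marginal R-squared moves from 0.02 to 0.15 over the same range, but it too mixes in time and covariates and does not isolate the intervention.

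The figures assume a random intercept, equal arms, no covariates and an equal shift in the three active arms. The level of about 0.5 depends on the correlation; the defect does not. It is confined to how results are reported, and it should be corrected before they are written up.

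**What to change.** Replace the effect-size sentence. For each outcome and post-baseline visit, report each of the three contrasts as a difference in change in scale points with a confidence interval. Use 97.5% intervals for the two primary outcomes, to match the 0.025 threshold in the sample size section. Add a version standardised by the pooled baseline SD, with a note that eligibility cut-offs on burnout and vigor may restrict that SD. If an R-squared is still wanted, give the marginal one and label it as a description of model fit.

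The cost is one sentence. The contrast estimates come from models already planned, and no data collection, test or sample size changes.
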